N = 65 Richartz et al. 1998 [8]	Prospective; Rejection during in-hospital period	1. Mean QT_C _= 449 ± 2 ms without rejection; 517 ± 11 ms with rejection (*p *< 0.001) 2. > 10% increase in QT_C _predicted rejection with sensitivity, 86%; specificity, 88%	1. Only observed rejection during hospitalization for transplant surgery 2. Analyzed only 3 ECGs per subject 3. ECG analyzers not blinded from clinical information about rejection	An increase in the QT interval predicts acute allograft rejection

N = 52 Kolasa et al. 2005 [9]	Retrospective; Long-term mortality over 7 yrs	Poorer survival over 7 yrs in subjects who had a > 10 ms per year change in their QT_C _interval on their annual ECG	1. Link to rejection not studied 2. Analyzed only one ECG per year	As little as a 10 ms change in the QT interval is linked to mortality

N = 200 Tenderich et al. 2006 [10]	Retrospective; Rejection during first 3 months	> 25 ms increase in QT_C _interval predicted acute allograft rejection with sensitivity, 77%; specificity, 96%.	1. Only analyzed 2 ECGs per subject 2. ECG analyzers not blinded from clinical information about rejection	Increase in QT interval predicts acute rejection during the period of interest

N = 587 Vrtovec et al. 2006 [11]	Retrospective; Long-term mortality up to 17 yrs	1. Patients with ≥ 10% increase in QT_C _interval between 1^st ^and 2^nd ^year post-transplant had 6.86 times higher risk of dying.2. ≥ 10% increase in QT_C _was the only independent predictor of long- term mortality on multivariate analysis 3. Trend was a decreasing QT_C _over the yrs suggesting sympathetic reinnervation	1. Link to rejection not studied 2. Analyzed only one ECG per year	An increase in the QT interval is linked to mortality

N = 71 Vrtovec et al. 2008 [12]	Retrospective; 1- year all-cause & SCD mortality in subjects with severe acute rejection	1. QT_C _was longer in SCD group than in survivors (475 ± 57 versus 437 ± 36 ms; *p *= 0.02) 2. Patients who had > 10% increase in QT interval during a severe acute rejection episode were at increased risk for SCD.	1. Limited to just patients with severe rejection; unable to tell whether increased QT interval could predict earlier, milder forms of rejection 2. Analyzed just 2 ECGs per subject (one at baseline 7 days after surgery, second at time of rejection)	An increase in the QT interval is linked to mortality

ms = millisecond; SCD = sudden cardiac death; QTc = QT interval corrected for heart rate

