## Methods/design

### Design

The NEW HEART study is a prospective, double-blind, multi-center descriptive research study. The primary aims of the NEW HEART study are to: 1) determine whether an increase in the QT interval during the first 6 months following heart transplant is a sensitive and specific biomarker for acute allograft rejection; 2) determine the timing of initial increased QT interval relative to biopsy-diagnosed stages of mild, moderate, and severe allograft rejection.

Secondary aims are to: 1) determine whether an increase in the QT interval during the first 6 months following heart transplant predicts mortality within the first year, and 2) explore additional ECG measurements that might predict acute allograft rejection or death.

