### Procedures

Participants will be recruited either while they are in the hospital for transplant surgery, or if that is inconvenient, during their first clinic visit following transplant surgery. After informed consent is obtained, demographic and clinical data will be collected by self-report and by medical record audit. At the time of each EMB, data from the medical record will be abstracted to confirm current medications, serum levels of anti-rejection medications, clinical data regarding EMB results, and other clinical data reflecting myocardial performance consistent with rejection status. Only one anti-rejection medication (tacrolimus) is associated with an increased QT interval. If a patient is on chronic tacrolimus therapy without a change in dosage, it should not interfere with the daily ECG monitoring measurement because we will be comparing each patient with him/herself and noting any change from the previous day's QT interval. However, we will track initiation or change in any QT-prolonging drug. On their website, the Arizona Center for Education and Research on Therapeutics [15] maintains a comprehensive list of QT- prolonging drugs that we have incorporated into the medications section of our electronic database system. Further, on a quarterly basis, we will continue to reference this website for new drugs as they come to market and update our data capture to include those associated with QT-prolongation.

The other drug class that patients may be taking is 3-Hydroxy-3-Methyl-Glutaryl Coenzyme A Reductase inhibitors (i.e., statins) which are known to shorten the QT interval. Thus, we will also monitor statin therapy. To insure patient safety, we will notify patients' transplant cardiologists within 48 h of the detection of any QTc interval exceeding the population 99th percentile for adult males (> 470 ms) or females (> 480 ms) [16].

At the time of informed consent and enrollment, subjects will receive the HeartView™ recorder and its companion Internet Transmitter, which will transmit the subject's ECG as described earlier. Subjects will be asked to record a 10-s 8-lead ECG daily for 6 months.

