### Analysis of ECG monitoring data

The ECG will be sent to a large server hosted by the UCSF Office of Academic and Administrative Information Systems (OAAIS). The server is a secure, highly redundant data center with 24/7 availability due to back-up generators that protect against power outages. The system provides nightly data backup. Investigators in the [name] Lab will access the ECG data by logging on with a username and password via a Virtual Private Network (VPN), which encapsulates data transfers between networked devices not on the same private network and keeps the transferred data private from other devices. Investigators who analyze the daily ECG data will be blinded from all information regarding the subject's clinical status and biopsy results. In addition, pathologists who grade the biopsies and clinicians who provide medical care in the transplant clinics will be blinded from the QT interval monitoring data.

QT and RR intervals will be made in a computer-assisted manner. The Aerotel measurement software provides a zooming feature to enlarge ECG waveforms for better visualization. In addition, electronic calipers are provided so that the researcher will select the appropriate waveform onset and offset points and the computer software will provide the interval value in milliseconds (ms). The QT interval will be measured from the onset of the QRS waveform to the end of the T waveThe end of the T wave will be defined as the intersection of a tangent to the steepest slope of the last limb of the T wave and the baseline (Figure 2) [18]. A standardized correction to account for the effect of HR will be applied (QT_C_). An increase in the QT_C _interval from the previous day of at least 25 ms that persists for 3 consecutive days will be considered abnormal [10].

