**Figure 2 F2:**
[figure not shown]
**Measurement of QT Interval**. A tangent is drawn to the steepest slope of the last limb of the T wave; the end of the T wave is the intersection of this tangent with the baseline.

To explore the potential diagnostic and prognostic value of additional ECG measurements, the following variables will also be measured on the daily ECG recordings: cardiac rhythm, heart rate, P wave and QRS duration, PR interval, QRS amplitude, and the interval from the peak of the T wave to the end of the T wave [19]. A prolonged T_PEAK _- T_END _interval is thought to represent heterogeneity of ventricular repolarization across the 3 layers of the myocardial wall [20] and has been associated with risk for sudden cardiac death from torsades de pointes [21].

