Specificity	Proportion of those without rejection who are negative for the ECG criterion

Positive Predictive Value	Proportion of patients with positive ECG criterion who have rejection

Negative Predictive Value	Proportion of patients with negative ECG criterion who do not have rejection

Predictive Accuracy	$\frac{\#\text{true positives}\pm \text{true negatives by the ECG criterion}}{\text{Total }\#\text{ of patients enrolled in the study }\times \text{ 1}00}$

Descriptive statistics (means ± SD) will be used to describe the average time period between the development of the ECG criterion and biopsy evidence of rejection. In addition, we will report the proportion of subjects who develop the ECG criterion (≥ +25 ms increase in QT interval from previous day lasting 3 consecutive days [10]) before, during, or after the stages of mild, moderate, and severe rejection.

The Kaplan-Meier method with the log-rank test will be used to estimate survival curves over one year and to compare all-cause mortality in patients who are positive or negative for the QT_C _criterion. Cox Proportional Hazard modeling will be used to control for baseline differences between groups and for tacrolimus use.

Logistic regression will be used with the dependent variables of rejection (yes/no) and all- cause mortality (yes/no). In both regressions, tacrolimus dosage (with "0" entered if the patient is not receiving tacrolimus) will be included as a covariate in the model. If any of the explorative variables are statistically significant, a multiple logistic regression model will be used including the ECG criterion of interest to determine whether additional ECG criteria are independent predictors of rejection and death.

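### The survival analysis names one QT predictor, a day-on-day 25 ms rule taken from a rejection study, so gradual QTc prolongation counts as negative when the aim is to predict one-year death

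*Protocol article*

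**What the plan says.** The Design section of the protocol article sets secondary aim 1: to "determine whether an increase in the QT interval during the first 6 months following heart transplant predicts mortality within the first year".

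The Statistical analysis section turns this into one split. Kaplan-Meier curves and the log-rank test are used "to compare all-cause mortality in patients who are positive or negative for the QT" criterion, and a Cox model adjusts that comparison for baseline differences and tacrolimus. Under Analysis of ECG monitoring data, the criterion concerns QTc lengthening: a change in this "interval from the previous day of at least 25 ms that persists for 3 consecutive days will be considered abnormal [10" (the closing citation is to reference 10). Table 2 gives the same definition.

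Table 1 lists reference 10 as a study of rejection in the first 3 months, with two ECGs per subject and no mortality result. Its three mortality studies measured other things:

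- **N = 587, mortality up to 17 years:** a QTc rise of at least 10% between the first and second post-transplant years, which "was the only independent predictor of long- term mortality on multivariate analysis".
- **N = 71, one-year mortality in severe rejection:** "Patients who had > 10% increase in QT interval during a severe acute rejection episode were at increased risk for SCD" (sudden cardiac death), and QTc level, 475 ± 57 ms in sudden deaths against 437 ± 36 ms in survivors.
- **N = 52, 7-year survival:** a change of more than 10 ms per year.

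The additional ECG variables to be explored against rejection and death are "cardiac rhythm, heart rate, P wave and QRS duration, PR interval, QRS amplitude, and the interval from the peak of the T wave" to its end. Neither this list nor Table 2 contains a QTc change from a patient's own baseline. The QTc level appears only in the Procedures section, where the transplant cardiologist is told of any QTc "interval exceeding the population 99th percentile for adult males (> 470 ms) or females (> 480 ms".

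**The concern.** The aim is about an increase in the QT interval over 6 months. The rule captures one form of increase: an abrupt step from one day to the next that then holds. A QTc that climbs by the same total amount over several days or weeks is also an increase, but the rule puts that patient in the negative group.

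If gradual prolongation carries any excess risk of death, those deaths fall in the comparison group and pull the hazard ratio towards 1. The trial could then report that an increased QT interval does not predict one-year death, when all it tested was a day-on-day step. The daily recordings needed to test cumulative change will already be in the database.

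**Working it through.** The article states no power, effect size or event count for the mortality aim, so there is no figure to reproduce. The check is whether the rule and a cumulative rise identify the same patients.

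**1. Noise-free arithmetic.** Reference levels are from Table 1: 437 ms (survivors), 449 ms (no rejection), 475 ms (sudden deaths).

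| Start level | 10% rise | Per day over 2 days | Per day over 7 days | 25 ms as % of start |
|---|---|---|---|---|
| 437 ms | 43.7 ms | 21.9 ms | 6.2 ms | 5.7% |
| 449 ms | 44.9 ms | 22.5 ms | 6.4 ms | 5.6% |
| 475 ms | 47.5 ms | 23.8 ms | 6.8 ms | 5.3% |

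Every daily step is under 25 ms once the rise takes 2 days or more, so the rule is not met. Conversely, a sustained 25 ms step is positive at under 6%, without reaching 10%. Neither measure contains the other.

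**2. With day-to-day noise.** The article gives no within-patient SD, so 5, 8 and 10 ms are assumptions. Simulation: 180 daily values, a linear 43.7 ms rise followed by a plateau, independent normal noise. A patient is positive if three consecutive days are all at least 25 ms above the day before them.

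| Duration of rise | SD 0 | SD 5 ms | SD 8 ms | SD 10 ms |
|---|---|---|---|---|
| 2 days | 0% | 44% | 59% | 77% |
| 3 days | 0% | 14% | 41% | 69% |
| 7 days | 0% | 0.7% | 20% | 56% |
| 30 days | 0% | 0% | 13% | 49% |
| No rise | 0% | 0% | 10% | 44% |

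At 5 ms the rule misses nearly all week-long rises. At 8 ms it misses most of them. At 10 ms it flags about half of the slow rises, but also 44% of patients with no rise, so it hardly separates the two.

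**3. Expected deaths.** The Background says first-year mortality reaches 13%: 325 × 0.13 = 42.25, so about 42 at most.

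**4. What dilution could cost (illustration only).** Suppose a share p of patients have a true risk marker with hazard ratio HR. The rule flags a share s of them and a share f of the others. The positive fraction is P = p·s + (1−p)·f.

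Hazard in positives = [p·s·HR + (1−p)·f] / P

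Hazard in negatives = [p·(1−s)·HR + (1−p)·(1−f)] / (1−P)

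Power = Φ(√(42·P·(1−P))·ln(diluted HR) − 1.96), two-sided 5%.

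Assume p = 0.20 and HR = 3. Analysed directly: √(42 × 0.16) × ln 3 − 1.96 = 0.89, power 81%. Through the rule with s = 0.50:

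- f = 0.04: P = 0.132, diluted HR 2.04, power 35%.
- f = 0.12: P = 0.196, diluted HR 1.62, power 24%.

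With s = 0.77 the range is 49–59%; with s = 0.25 it is 7–15%. The documents give none of p, HR, s or f.

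**The case against.** The strongest reply is that nothing here is misstated. One pre-specified criterion applied to both rejection and death is a coherent choice, the aim is secondary, and a condensed article may leave further codings of a measured variable to the full plan. Table 2 also types ΔQTc as continuous. Part of this stands: no figure is wrong. But the article does fix the mortality predictor and itemises the exploratory ECG variables, and the quantity that Table 2 calls continuous is still a change from the previous day.

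A reader might infer more than the documents support:

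- **That a known mortality risk goes untested.** Table 1 does not show one for this setting. The first-to-second-year rise and the annual change cannot be observed in 6 months of ECGs and relate to survival over 7 to 17 years. The one-year study concerns sudden death in severe rejection, against a day-7 baseline. Enrolment here runs to six weeks after surgery, so an early-recordings baseline does not reproduce that either.
- **That QTc level should be a main mortality predictor.** A steadily long QTc is not an increase, so it falls outside the aim. Values above 470/480 ms also trigger notification, which may alter care and confound any association with death.
- **That the rule could make prolongation look protective.** The documents give no basis for expecting a hazard ratio below 1; dilution towards 1 is the supported effect.
- **That only the 25 ms rule is tested against death.** Other ECG variables, including the T-peak to T-end interval, are tested too. The rule is the only QT-interval predictor named.

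No passage says that QTc rises gradually before death, so the linear ramp is an assumption, as are the noise SDs.

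**Conclusion.** The point holds as a mismatch between a secondary aim and its only named QT predictor. The aim asks about an increase over 6 months. The rule detects an abrupt step, rests on a rejection study with two ECGs per subject, and by arithmetic alone excludes an even 10% rise over 2 days or more.

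The direction of the effect, dilution towards no association, follows if gradual prolongation carries excess risk. Its size cannot be fixed from the document: the share of 7-day rises flagged runs from about 1% to 56% as the assumed SD goes from 5 to 10 ms, and the power figures rest on assumed prevalence, hazard ratio and overlap. The point does not rest on a proven one-year risk. A null mortality result would be ambiguous as the plan stands, and the data to make it less so are already being collected.

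**What to change.** In the Statistical analysis section and Table 2, keep the 25 ms criterion and add one pre-specified secondary predictor of one-year mortality: QTc change from the patient's own early baseline.

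- Define the baseline, for example as the median of the first 7 recordings, and measure change from it with a running median to damp daily noise.
- Enter it in the Cox model as a continuous, time-updated covariate. State that the last value is carried forward once monitoring ends at 6 months, because deaths are counted to one year.
- Report a rise of at least 10% as a supporting cut-off.
- If QTc level is reported, label it exploratory and note that values above 470/480 ms trigger notification and may alter care.
- Limit any negative conclusion on mortality to the measures tested.

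The cost is wording and a little analysis, with no new data, visits or staff. The downside is one further secondary test on at most about 42 deaths, and probably fewer, since enrolment requires clinical stability. No change to the notification rule or to care is proposed.

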## Background

The prevalence of American adults living with a heart transplant was 20,369 in 2009, the most recent year for which complete data are available [1]. Acute allograft rejection is a major cause of early mortality, a rate that reaches 13% in the first year after heart transplantation in adults [1,2]. According to the 2011 annual United States data published from the International Society for Heart Lung Transplantation Registry, 26% of heart transplant recipients have at least one rejection episode within the first year following transplant surgery [2]. Acute rejection remains the most common cause of morbidity and rehospitalization. Jalowiec [3] reported that 64% of heart transplant recipients were rehospitalized during the first year after transplant surgery (median length of stay, 16 days), and 37% were rehospitalized more than once. Rejection is also a primary cause of urgent re-transplantation, a situation that is perceived by some to be morally unfair because these patients are allowed a second transplant while others are waiting and often dying before receiving their first transplant. Thus, the financial, physical, and emotional toll associated with acute rejection is significant.

In order to detect the early stages of rejection so that more aggressive and early immunosuppressant therapy can be initiated, frequent biopsies of heart tissue are performed (typically, weekly or every other week in the first three months and then monthly or every other month during the first year). Although endomyocardial biopsy (EMB) is not a perfect "gold standard" for a correct diagnosis of acute allograft rejection, it is considered the best available test and thus, it is the current standard practice. Unfortunately, EMB is an invasive and costly procedure that is not without risk [4,5]. If a simple noninvasive biomarker could be identified to detect the early stages of acute rejection, it might be possible to reduce the number of invasive biopsy procedures and to initiate earlier therapy that might prevent death from severe rejection.

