### Sample

A sample of 325 adult heart transplant recipients will be recruited from the Columbia University-New York Presbyterian Medical Center (CU-NYP), the University of California, Los Angeles (UCLA), and Cedars Sinai Medical Center (CSMC) in Los Angeles, CA. Respectively, demographic characteristics at these sites are: male (68.9%, 75.7%, and 79.7%); White (53.1%, 59.1%, 73.4%); Black (20.3%, 9.4%,12.5%); Latino (14.5%, 19.9%, 9.4%) and Asian (11.3%, 10.5%, 3.1%) [1]. Inclusion criteria are: 1) ≥ 18 years of age, 2) first heart transplant surgery within six weeks of their transplant surgery, 3) not enrolled in other research studies that conflict with the study design, 4) clinically stable at time of enrollment (i.e. no clinical symptoms of allograft impairment with ejection fraction ≥ 45%).

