### Diagnosis of acute allograft rejection

Rates of acute allograft rejection have varied, but the most recent rates of rejection in the first 6 months after transplant are reported to be 25 to 35% [2]. The diagnosis of acute allograft rejection is made by an EMB which will be performed in the hospital cardiac catheterization laboratory at each site. Generally, 3-6 biopsy specimens of the right ventricular endocardium are taken to minimize false negative tests. Each site will follow its own acute rejection surveillance protocol. In general, these protocols require weekly or biweekly EMBs during the first two to three post-transplant months. After that time, biopsies are performed less frequently, based on clinical judgment and risk of rejection. At each site, EMBs will be graded by clinical pathologists experienced with the heart transplant population and using the International Society of Heart and Lung Transplantation standards for acute rejection. Although early reports indicated inter-operator variability in the interpretation of EMB results [22], the use of the standardized grading system has improved the reliability and validity of the measurement. Current variability in interpretation of biopsy results occurs mainly in the diagnosis of Grade 2 rejection by local pathologists which may be misinterpreted in the presence of endocardial infiltrates called Quilty lesions [23,24]. To control for potential variability, we will monitor and record clinical and hemodynamic indicators of myocardial performance, which are obtained at the time of each biopsy or at regular clinical assessments, to support the biopsy interpretation, particularly regarding Grade 2 rejection. Such a multi-factorial approach to identification of rejection has been recommended [24].

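### Screening seven exploratory ECG measures for significance and refitting in the same patients is too weak a basis for naming independent predictors of rejection or death

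*Protocol article*

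**What the plan says.** The section on analysis of ECG monitoring data lists the extra measures: "cardiac rhythm, heart rate, P wave and QRS duration, PR interval, QRS amplitude, and the interval from the peak of the T wave" to its end. That is seven. Table 2 gives rhythm four categories and treats the other six as continuous.

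The Statistical analysis section relates them to two outcomes: "Logistic regression will be used with the dependent variables of rejection (yes/no) and all- cause mortality (yes/no"), with tacrolimus dose as a covariate in both. It then sets the decision rule: "If any of the explorative variables are statistically significant, a multiple logistic regression model will be used including the ECG criterion of interest". The purpose of that second model is "to determine whether additional ECG criteria are independent predictors of rejection and death".

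The Design section words the matching secondary aim more softly, as to "explore additional ECG measurements that might predict acute allograft rejection or death". The Discussion says only that other useful ECG parameters may emerge and that meeting the study's aims may support a randomised trial.

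**The concern.** The second model reads as a check on the first, but both use the same patients. A measure gets into the second model because it was already significant in these data. Its second p-value and odds ratio are therefore conditional on that selection. Adjusting for the QTc criterion deals with overlap between the measure and QTc; it does not deal with chance. Selection also favours overestimates, so the retained coefficients tend to be too large.

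The rule opens if any one of fourteen tests is significant, and what comes out is named an independent predictor. At stake is how far a reader, or the designers of a later trial, can rely on a measure named in this way.

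**Working it through.** The article gives no alpha or error rate for this step, so there is no figure of its own to reproduce. The check asks how often the two steps name a predictor when none of the seven measures has any effect.

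**Inputs from the article**
- Seven measures and two outcomes: 7 × 2 = 14 screening tests.
- Sample: "A sample of 325 adult heart transplant recipients will be recruited".
- Rejection: "the most recent rates of rejection in the first 6 months after transplant are reported to be 25 to 35" per cent. 30% was used, and 25% in one run.
- Mortality: "a rate that reaches 13% in the first year after heart transplantation in adults", read as first-year mortality. 0.13 × 325 ≈ 42 deaths.

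**Assumptions, not in the article**
- Two-sided alpha of 0.05, with 0.01 and 0.10 as a range.
- No true effect of any of the seven measures.
- A common correlation among the measures of 0 to 0.7.
- Only the significant measures enter the second model. This is the natural reading, but the text does not say so outright.

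**Step 1: the screen alone, tests independent.** The chance of at least one false positive is 1 − (1 − α)^k.
- One outcome, α = 0.05: 1 − 0.95^7 = 30.2%.
- Both outcomes, α = 0.05: 1 − 0.95^14 = 51.2%.
- Both outcomes, α = 0.01: 13.1%. At α = 0.10: 77.1%.

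**Step 2: screen plus refit, simulated.** N = 325. Each measure was screened by a likelihood-ratio test with tacrolimus in the model, and rhythm had four categories. Survivors were refitted together with tacrolimus and the QTc criterion. The criterion was positive in 30% of patients and linked to each outcome with a log odds ratio of 1.0. A study counts as false if any survivor stays below alpha. The first four rows have 1,500 runs each and the last two 1,000.

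| Setting | Screen opens, either outcome | False predictor, rejection | False predictor, either outcome |
|---|---|---|---|
| correlation 0 | 52.5% | 24.9% | 44.6% |
| correlation 0.3 | 49.7% | 22.0% | 39.8% |
| correlation 0.5 | 47.9% | 18.0% | 34.4% |
| correlation 0.7 | 36.9% | 10.6% | 20.3% |
| correlation 0, rejection 25% | 56.3% | 27.1% | 48.2% |
| correlation 0.3, α = 0.01 | 14.0% | 5.4% | 10.7% |

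Monte Carlo error is small: √(0.4 × 0.6 / 1500) ≈ 1.3 percentage points.

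The share of opened screens that still end in a false predictor is 44.6/52.5 = 85% at correlation 0, 39.8/49.7 = 80% at 0.3, 34.4/47.9 = 72% at 0.5 and 20.3/36.9 = 55% at 0.7. The refit removes little of the error at low correlation and more at high correlation.

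**Step 3: sensitivity.** A separate run at correlations 0, 0.3 and 0.6 gave 43%, 34% and 24% over both outcomes. A simpler simulation (no tacrolimus, two-level rhythm, correlation 0 or 0.3) varied the strength of the QTc criterion and gave 26 to 48% over both outcomes. For rejection alone it gave 20 to 29% with a weak criterion, but 7 to 10% if the criterion has the 77% sensitivity and 96% specificity shown in Table 1. A strong criterion combined with high correlation was not simulated; it could fall below 20%.

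**Step 4: the alternative.** With one full model for rejection, the joint test was falsely positive in 5 to 8% of simulated null studies, and Holm-adjusted naming in 5 to 7%. Error over both outcomes needs adjustment over all fourteen tests. Bonferroni at 0.05/14 = 0.0036 gives 1 − (1 − 0.05/14)^14 = 4.9% if the tests are independent.

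**The case against.** The strongest reply is that this is declared exploration. The aim, the section on ECG measurements and the analysis rule itself all use exploratory wording, and the Discussion claims only possibilities. Unadjusted testing is common in such work, and a significance level or multiplicity rule may properly sit in a full protocol or analysis plan that is not shown. The second model can also be read as asking only whether a measure adds to QTc, with no claim of confirmation.

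Much of this stands. It lowers the weight of the point, and the missing alpha is not itself a fault. What remains is that the Statistical analysis section does fix the screen-then-refit rule, and there the purpose is to determine independent predictors, which goes further than exploring.

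A reader might infer more than the article supports:
- **That a false predictor in a quarter to a half of studies is a property of the plan.** The rate rests on an assumed alpha, on no true effects, on pooling two outcomes and on unknown correlations. Some correlation is likely, since Table 2 starts the PR interval at the onset of the P wave and so includes P wave duration.
- **That the secondary aim is itself worded as a conclusion.** It speaks of measures that might predict.
- **That the main result is compromised.** The primary QTc analysis does not pass through this step.

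**Conclusion.** The point holds, at modest weight. A significance screen followed by a refit in the same 325 patients does not justify the label the article attaches to its output. Under the global null and an assumed two-sided 0.05, about 20 to 48% of studies would name at least one false predictor of rejection or death. The figure is nearer 20% if the measures are strongly correlated, and about 11% at alpha 0.01 with correlation 0.3. These rates take the natural reading of which measures enter the second model and, in the main simulation, a moderately predictive QTc criterion. The inflation of retained coefficients follows from the selection itself, whatever alpha is used.

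**What to change.** In the Statistical analysis section, remove the univariable significance gate and replace it as follows.

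- **Rejection.** Fit one pre-specified model with the QTc criterion, tacrolimus and all seven measures. Rhythm is a 3-df term, so the measures use 3 + 6 = 9 df and the model has 11 coefficients besides the intercept. At 25 to 35% rejection that is about 81 to 114 patients with rejection, or 7.4 to 10.3 per coefficient. Report one joint likelihood-ratio test on the 9 df, and Holm-adjusted p-values beside the unadjusted ones.
- **P wave.** State how P wave duration and PR interval are handled in recordings without a P wave, since Table 2 allows atrial fibrillation.
- **Mortality.** The same 11 coefficients on about 42 deaths leave 42/11 ≈ 3.8 deaths each, which is too few for an ordinary full model. Use a penalised or reduced model, specified in advance. The penalised fit was not simulated here.
- **Wording.** Call a measure an independent predictor only if it is significant after adjustment. If the claim covers both rejection and death, the adjustment must span both, because Holm within each outcome does not control error over the two. Report everything else as hypothesis-generating.

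The cost is analysis wording and a little programming, with no new data. Intervals will be slightly wider, and a weak individual measure will need stronger evidence before it is named. At the least, the wording change alone would bring this section into line with the exploratory aim.
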